### Assessment of objectives

The study adopts the National Institute for Health Research Health Technology Assessment (NIHR HTA) definition of a feasibility study [28]. The primary objective will be to assess the integrity of the study protocol to determine the feasibility of conducting a larger, appropriately powered trial. The assessment of feasibility will be determined by measuring eligible numbers, the recruitment rate per centre, the spectrum of disease among recruits, reasons for non-recruitment, compliance with vocational rehabilitation in the intervention group and with usual care in controls and the completeness of follow-up of the primary endpoint. The study will also enable us to determine whether participants can be randomised to the intervention and the likely effect on drop out of randomisation to the control group (i.e. whether patients randomised to receive no vocational rehabilitation are more likely to withdraw).

The feasibility objectives will be measured as identified in Additional file 1.

Determination of acceptability in TBI patients, staff and employers will be measured by interviewing up to 30 trial participants, 10–20 employers and the therapists providing the intervention (*n* = 4) to seek their views on the interventions (ESTVR vs UC) and in-patients and staff only, their views on recruitment and the acceptability of randomisation. We will seek to understand what service interventions are most valued in practice by an employee with TBI and which by an employer. We anticipate that we will interview between 10 and 20 employers (not all TBI participants will agree to employer contact), 15 NHS staff (5 from each centre), 4 ESTVR trained therapists and 30 trial participants (15 in each arm of the trial). It was felt that this would provide sufficient data to inform the feasibility objectives and identify issues and strategies to inform the design of the definitive trial.

The combination of the qualitative process data, plus the feasibility trial data will help to determine the integrity of the study protocol and allow us to estimate parameters necessary to calculate the sample size for a larger trial (e.g. rate of return to work at 12 months in control group).

This feasibility trial will enable us to measure recruitment, retention, the viability of delivering the intervention and measurement of the effectiveness and cost effectiveness of ESTVR plus usual NHS rehabilitation vs usual NHS rehabilitation.

As the likely primary measure of effectiveness for the main trial is work status at 12 months defined as competitive employment (full- or part-time paid work in an ordinary work setting, paid at the market rate) [29], we will record as the success criteria for the intervention at 12 months post randomization, the proportion of persons returned to and retained in:work in the same role with an existing employer;work in a different role with an existing employer;work with a different employer, i.e. new work, same or a different role; andself-employed work.

This will be collected by postal questionnaire using a series of bespoke work focussed questions.

Secondary measures of effectiveness collected at 3-, 6- and 12-month post randomisation include hospital anxiety and depression scale [30], extended activities of daily living [31], community integration questionnaire [32], EuroQol EQ-5D-3 L [33], work productivity and activity impairment questionnaire [34], carer-strain index [35], self-efficacy question from the work ability index [36] and data on the use of health and social care resources, including GP, nurse, therapists, employment services and medication use. At 12 months, the Glasgow outcome scale score will be collected as a measure of TBI recovery. This will help determine the sensitivity of measures/their value and any change related to the ESTVR intervention.

The schedule of assessments is shown in Table 1

**Table 1 Tab1:** Schedule of assessments for patients and carers

Measure		Follow-up time points		
	Baseline	3 months	6 months	12 months
Schedule of assessments (patients)				
Demographic information	☑	-	-	-
Duration PTA	☑	-	-	-
GCS score	☑	-	-	-
Duration unconsciousness	☑	-	-	-
Specific VR-focused questions	☑	☑	☑	☑
EQ-5D-3 L (Euro-QOL)	☑	☑	☑	☑
Hospital anxiety and depression scale (HADS)	☑	☑	☑	☑
Nottingham extended activities of daily living (NEADL)	☑	☑	☑	☑
Community integration questionnaire (CIQ)	☑	☑	☑	☑
Resource use of health and social care	☑	☑	☑	☑
Self-efficacy—single question from work ability index	☑	☑	☑	☑
Work productivity and activity impairment questionnaire V2 (WPAI)	☑	☑	☑	☑
Glasgow outcome scale score (GOS)				☑
Schedule of assessments (carers)				
Carer strain index (CSI)	☑	☑	☑	☑
Specific impact on carer’s work questions	☑	☑	☑	☑

The proposed flow of participants through the study is shown in Fig. 2.

**Fig. 2 Fig2:**
[figure not shown]
Proposed flow of participants through the feasibility trial

### Sample size justification

The sample size was based on an expectation to recruit approximately one third of patients fitting the eligibility criteria, e.g. 100 participants from 300 patients approached over 12 months. This will enable us to estimate the recruitment rate to within +/−6 % (with 95 % confidence) and the attrition rate to within +/−7 % (with 95 % confidence) (assuming attrition rate ≤15 %). The trial will recruit for 12 months. We anticipate that not all TBI participants will have or be willing to pass on carer details; however, we believe that at least 30 % of carers identified by TBI participants’ can be recruited.

### Data management

Personal data, case report forms and participant questionnaires will be treated as confidential documents and held securely in accordance with regulations at the Lancashire Clinical Trials Unit for trial participants and data from the service evaluation will be stored with the chief investigator at the University of Nottingham. Source data may include but are not limited to, consent forms, baseline data forms and current occupational therapy treatment records, audio recordings and interview transcripts from the process evaluation studies. A case report form may also completely serve as its own source data. Data will be restricted to those personnel approved by the chief or local principal investigator and recorded on the *Trial Delegation Log*.

### Analysis

Estimation of eligibility, consent and attrition rates etc. (both overall and by subgroups, e.g. site) will use descriptive statistics, supported by 95 % confidence intervals.

Effectiveness outcomes will be described at each time point and compared between groups using descriptive and inferential methods for categorical, continuous and/or ordinal health outcome measures using an intention-to-treat approach, although imputation of missing outcome data will not be performed for the primary analysis; any inferential analysis of outcomes will use 95 % confidence intervals (no *p* values will be reported). Exploratory logistic regression will be used to provide estimates of intervention effectiveness, adjusted for baseline factors previously found to be related to work return (and therefore considered to be clinically important) at 12-month post-randomisation. Investigation of the distribution of responses for health outcome measures and of patterns in work status over time will be performed to inform the design (primary outcome, follow-up duration, analysis, sample size etc.) of a future trial. Key parameters (e.g. percentage in work at 12 months in control arm) will also be estimated (with confidence intervals) to inform the design of the potential future trial. Although imputation of missing data will not be performed, we will describe the nature and extent of missing data. Relationship between return to work, mood, wellbeing, function, work capacity, social participation, quality of life and carer strain will be explored in complete case respondents.

Data will be analysed using SPSS and Stata. A detailed statistical analysis plan will be written by the trial statistician, in consultation with the Study Steering Committee and Trial Management Group, prior to un-blinding of the data.

### Embedded qualitative and quantitative sub studies

In a series of embedded qualitative and quantitative studies, we will explore the following:Factors that determine how much VR intervention is delivered. We will maintain detailed records of each session of the ESTVR intervention delivered by each OT using a proforma developed for use in the original cohort comparison and described elsewhere [22] and analyse the content retrospectively on a case-by-case basis to identify core components of the intervention for future trial design and replication. Features of treatment in those with successful and unsuccessful work outcomes will be identified and described using a *content of treatment* proforma [22]. Further detail about the intervention will be ascertained during participant interviews in 15 trial participants randomised to receive ESTVR.Practical issues relating to the deployment of the intervention will be discussed at site monitoring visits using a topic guide to include practical issues related to the screening, recruitment and consent of participants and deployment of the intervention in each group. The Nottingham therapist who developed the original ESTVR intervention and who recruited participants with TBI in the original cohort comparison study [21] will visit the newly trained ESTVR therapists and recruitment staff in each centre every 3 months. She will discuss intervention cases, review case notes and *content of treatment* proformas and monitor ESTVR fidelity by cross-referencing with data from the original study and 20 years’ clinical experience in model delivery.Issues relating to the training provided and required for NHS staff and participants to deploy the VR intervention. The ESTVR trained therapists views of the acceptability and usefulness of the ESTVR training, manual and mentoring will be explored in four occupational therapists trained to deliver the intervention. Their views on perceived changes in practice resulting from training and the anticipated and actual effects (including costs) of ESTVR implementation on supporting services will be ascertained. In addition, participants’, employers’ and NHS staff views of the factors likely to affect the way ESTVR vocational rehabilitation can be implemented and delivered clinically in the NHS will be explored in 15 NHS staff with a role in managing, commissioning or delivering TBI rehabilitation (five each per site) identified by local PIs and therapists involved in the ESTVR delivery, 15 TBI participants randomised to receive ESTVR and up to 10 of their employers. They will be contacted by letter and invited to participate.Finally, to describe the content of usual care and ESTVR in the two groups and the extent to which ESTVR occurs in usual care (the routine rehabilitation of people with TBI), we will use a questionnaire developed for a related mapping study [15] which allows components of the VR intervention delivered in any service to be mapped against a *gold standard* (best practice recommendations for vocational rehabilitation for people with long-term neurological conditions) [13]. This will enable us to identify and describe components of VR service delivery in usual care and any differences between usual care and the ESTVR model in the proposed study. VR providers in health services in each centre will be identified using data from the original mapping study plus local knowledge of PIs and therapists in each centre, to identify usual care providers. We will ask identified services to complete the questionnaire at the study outset and again at the end of the intervention period. This will capture data about the actual VR components offered by services in usual care at the study outset and allow us to describe whether usual care changed during the course of the study. As this is feasibility study, this descriptive data will allow us to characterise the variation in usual care across the three centres and pre-set criteria for planning a larger study. In addition, during participant interviews described above, the extent to which support similar to ESTVR is delivered in usual care will be explored among participants interviewed from the UC group (*n* = 15).To identify primary outcomes of VR that are important to service users, service providers and employers, we will conduct focus groups and interviews with people from each category. We will interview trial participants prior to randomisation to explore what outcome from vocational rehabilitation would important to them. We will also hold three focus groups, one with TBI survivors (*n* = 10) of mixed severity and time since injury identified in partnership with existing services; one with employers (*n* = 10) identified from local business networks and large employers, human resource departments, disability employment advisors, the chamber of commerce, the Federation of Small Businesses and the Employers Forum for people with disability; and one with TBI service providers in health (*n* = 10) (including doctors, nurses, and therapists). Focus groups will explore the notion of important outcomes for people with TBI following a health-based vocational rehabilitation intervention. The success criteria defined in the outcomes section of the trial plan, which are provisional and subject to change, will be presented to promote discussion about the best endpoint and nominal group technique [37] used to prioritise identified outcomes.

Using data iteratively from the qualitative interviews, focus groups and actual outcome data from our feasibility trial, we will identify *primary outcomes* of importance to explain the impact of health-based vocational rehabilitation interventions in terms of “what matters to people with TBI, what matters to TBI service providers and what matters to employers of people with TBI”.

Interviews will be digitally recorded and field notes made to capture inaudible or other contextual information. All interviews will be fully transcribed and analysed using the framework approach. The findings will inform the design of the definitive trial, the delivery of the ESTVR and the challenges likely to be faced in sustaining its delivery in the longer term.

### Health economic evaluation

This feasibility trial will allow us to determine whether we can we effectively capture economic data from people with TBI and the completeness of economic data collection needed to undertake a cost-effectiveness study comparing the overall per patient cost and effectiveness of the ESTVR, to usual care in managing working age TBI survivors. The feasibility of collecting cost and benefit data will be assessed from a health (NHS) and social care (personal social service (PSS) system) perspective to determine the frequency and costs of all NHS, social services and medication provided and from a societal perspective to determine the frequency and cost of TBI on the carers work status, the employer and government employment services, e.g. benefits and disability employment advisors.

A preliminary cost analysis will compare the overall and incremental costs for the intervention to standard practice. This sub-study will identify the resource items likely to change as a result of the ESTVR intervention, explore the practicality of collecting necessary data, and find appropriate unit cost sources to value them. In particular, we will test using bespoke patient questionnaires to capture patient costs and the ease with which patients’ self-report patient and carer costs. We will also attempt to capture the costs to employers of making *reasonable adjustment* for TBI survivors returning to work. These may include pieces of equipment or modifications to the workplace, changes to the employee’s role and responsibilities that mean other input is needed, e.g. help from employees, additional breaks, greater flexibility in terms of hours and support or supervision. However, in this feasibility study, our starting point will be to record and describe these changes and attempt to quantify them using local (data from interviews with participants and employers where reasonable adjustment has been made) and published sources.

Should data be sufficient to proceed to analysis, the cost analysis will be combined with outcome measures to perform preliminary cost-effectiveness (CEA) and cost-utility analyses (CUA). CEA and CUA produce ratio statistics in terms of cost per unit of outcome (the outcome being the percentage difference between groups of participants in work or education) and cost per quality adjusted life year (QALY), area under the curve analysis with EQ-5D-3 L values will be used to calculate QALYs. Point estimate incremental cost effectiveness ratios (ICERs) will be generated where appropriate (e.g., where the new intervention is both more expensive and more effective or less costly and less effective. Uncertainty surrounding the economic results will be explored using cost-effectiveness acceptability curves (CEACs) [38].

### Trial management and oversight

A study steering committee is in place composed of independent representatives (3:1) from the medical, academic and lay communities and representatives from the Trial Management Group. Ethical approval for this study is provided by the Northampton Research Ethics Committee (13/EM/0353) and management approval has been obtained from the trial sites.

### Safety monitoring and adverse events

As this is a feasibility trial, the side effects of the intervention are as yet unknown. We will identify these as part of this study to inform future trial design. Therefore, we propose to collect outcome data related to the intervention from participants and trial therapists including accidental injury resulting from non-compliance with equipment or work place adaptations recommended by the FRESH occupational therapists, work accidents resulting in injury requiring hospital admission, incidents of aggression (defined as excessive verbal aggression, physical aggression against objects, physical aggression against self and physical aggression against others) of the participant towards the researcher, staff or others (e.g. work colleagues), attempted suicide. All adverse outcomes will be recorded and monitored until resolution, stabilisation, or until it has been shown that the study intervention is not a likely cause.

The CI and the sponsor shall be informed immediately of any serious adverse outcomes and the seriousness and causality will be reviewed by the chief investigator in conjunction with the medical practitioner chair of the date monitoring and ethics committee which is integral to the study steering committee.

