### Intervention and comparator

#### Early specialist traumatic brain injury vocational rehabilitation (ESTVR)

Participants (TBI patients) randomised to the intervention group will receive all usual NHS rehabilitation interventions but, in addition, will receive ESTVR (as required) targeted at job retention.

ESTVR is an early, TBI specialist, vocational rehabilitation job retention model. It was developed in Nottingham by an occupational therapist and is routinely delivered as part of usual NHS rehabilitation by the Nottingham Traumatic Brain Injury Service. It was evaluated in a single-centre cohort comparison study [27], and the results suggested a positive influence on 12-month work outcomes in those who received it. ESTVR is a case coordination model [24] based on best practice guidelines for vocational rehabilitation following acquired brain injury [19]. It is delivered by an occupational therapist, supported by a health-based case manager both of whom have knowledge and skills in working with people with a TBI and in vocational rehabilitation. Most interventions are delivered in the community.

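### Adverse outcomes have a second reporting source in the ESTVR arm only, so counts pooled over sources should not be read by arm

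*Protocol article*

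**What the plan says.** The section Safety monitoring and adverse events gives its purpose as follows: "the side effects of the intervention are as yet unknown. We will identify these as part of this study to inform future trial design". It names two sources: "we propose to collect outcome data related to the intervention from participants and trial therapists". The listed outcomes begin with "accidental injury resulting from non-compliance with equipment or work place adaptations recommended by the FRESH occupational therapists" and go on to "work accidents resulting in injury requiring hospital admission, incidents of aggression" and attempted suicide.

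The article describes trial therapists in one arm only. Intervention participants "will receive all usual NHS rehabilitation interventions but, in addition, will receive ESTVR (as required) targeted at job retention", and of ESTVR it says: "It is delivered by an occupational therapist, supported by a health-based case manager". Under Control: usual NHS rehabilitation, controls use ordinary health and social care services, and no professional who reports to the trial is named for them. Under Assessment of objectives, the therapists providing the intervention number four.

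The contact common to both arms is described under Follow-up: a masked research assistant in one centre and postal questionnaires in the other two. Under Analysis, between-group comparison is specified for effectiveness outcomes; harms are not mentioned.

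**The concern.** A participant in the ESTVR arm can have an event recorded because they report it or because the therapist does. For a control, the safety section names only the participant. The extra source is also well placed: the ESTVR section has the therapist visiting worksites, liaising with employers and reviewing progress, and the section on embedded sub studies has every ESTVR session recorded and case notes reviewed at three-monthly visits. Work accidents and aggression towards colleagues are events that such a therapist may hear of even when the participant does not mention them.

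Work accidents, aggression and attempted suicide can occur after brain injury in either arm. Calling any excess a side effect of ESTVR calls for a background rate collected in the same way. If the two sources are merged into one count per arm, part of any excess in ESTVR may be fuller capture, and that excess could be carried into the design of the definitive trial.

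**Working it through.** **The plan's own figures.** The article states no adverse-outcome rate, reporting sensitivity or harms sample size, so there is no harms figure to reproduce. Its stated precision concerns recruitment and attrition and does not bear on this point.

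**Which events and sources exist in which arm.**

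| | ESTVR | Control |
|---|---|---|
| Participant report | yes | yes |
| Trial therapist report | yes | no such therapist described |
| Injury from not following FRESH recommendations | possible | not possible |
| Work accident with admission, aggression, attempted suicide | possible | possible |

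The asymmetry follows from setting the safety section beside the two sections describing the arms.

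**How large the distortion could be.** All inputs below except the total sample size are assumptions.

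- True event risk p = 0.10 in both arms, so there is no real difference.
- n = 51 per arm, from the 102 in the abstract if allocation is 1:1.
- Participant sensitivity s_p from 0.3 to 0.9, the same in both arms.
- Therapist sensitivity s_t from 0.3 to 0.8.
- The two sources report independently.

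Probability that a true event is recorded:

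- Control: s_p
- ESTVR: 1 − (1 − s_p)(1 − s_t)

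The recorded ratio is [1 − (1 − s_p)(1 − s_t)] / s_p. The true risk p cancels from it.

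- Smallest (s_p = 0.9, s_t = 0.3): (1 − 0.1 × 0.7)/0.9 = 0.93/0.9 = 1.03.
- Middle (s_p = 0.5, s_t = 0.5): (1 − 0.5 × 0.5)/0.5 = 0.75/0.5 = 1.50.
- Largest (s_p = 0.3, s_t = 0.8): (1 − 0.7 × 0.2)/0.3 = 0.86/0.3 = 2.87.

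Expected recorded events in the middle case:

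- Control: 51 × 0.10 × 0.5 = 2.6
- ESTVR: 51 × 0.10 × 0.75 = 3.8

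**Restricted to participant reports.** Both arms then have detection probability s_p, and the expected ratio is s_p/s_p = 1.0.

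**Sensitivity to the independence assumption.** If therapists tend to hear of the same events that participants report, the ratio is closer to 1. In the extreme, with s_p = s_t = 0.5 and complete overlap, ESTVR detection is 0.5 and the ratio is 0.5/0.5 = 1.0.

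**The case against.** The strongest reply is that no between-arm comparison of harms is planned. The Analysis section compares effectiveness outcomes, and the safety section sets out to find unknown side effects of a new intervention. For that purpose, asking those who deliver it is sensible because it raises sensitivity, and an item tied to their recommendations is to be expected. This stands: using therapists as a source is not a flaw. What remains is that the same list contains events with a background rate in both arms, and the article gives no rule for keeping the sources apart when those events are summarised.

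A reader might go further and infer any of the following. The article does not support them.

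- *Harms cannot be compared at all.* Participants in both arms are a named source, so participant-reported events possible in both arms can be compared.
- *Events are over-recorded in ESTVR.* Nothing suggests that false events are recorded. The issue is more complete capture relative to control.
- *Background events will be attributed to ESTVR.* The safety section provides for follow-up of adverse outcomes until resolution, stabilisation or exclusion of the intervention as a likely cause. Serious outcomes have their causality reviewed by the chief investigator with the medical chair of the monitoring committee. That addresses attribution, though it does not equalise capture.
- *Controls are never asked, because Table 1 has no adverse-outcome item.* The article condenses a fuller protocol, and reporting forms and prompts may be set out there. The missing row proves nothing.

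It is also fair to say that the masked research assistant could observe aggression in either arm at the face-to-face centre, although the other two centres use post. The expected counts are small too: in the middle case, about 4 against 3 events could not support a conclusion about harm in either direction.

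**Conclusion.** The point holds as a limit on interpretation; it is neither a contradiction nor a wrong figure. On the article's text, one of the two sources and one of the listed events belong to the ESTVR arm only. Counts pooled over sources would tend to be more complete there and should not be read by arm as evidence of side effects.

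The direction rests on reading trial therapists as those delivering ESTVR, the only ones the article describes. The size is unknown. The range of 1.03 to 2.87 depends wholly on assumed sensitivities and independent reporting, and the bias is negligible if participants report most events themselves. The neutral ratio for participant reports assumes that participants report equally well in both arms. Since they know their allocation, that is plausible but not guaranteed.

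No sample-size figure or planned effectiveness analysis is affected. The change is worth making because it is cheap and serves the section's own stated aim.

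**What to change.** In Safety monitoring and adverse events:

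1. State that the same closed adverse-outcome questions are asked of participants in both arms at the existing 3-, 6- and 12-month follow-ups. If the full protocol already provides this, say so in the section.
2. Record the source of each report (participant or trial therapist).
3. Base any between-arm description on the common participant-reported route, limited to events possible in both arms.
4. List therapist-reported events, and the item on recommended equipment and adaptations, separately as descriptive data for the ESTVR arm only.

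The cost is a slightly longer questionnaire at three existing contacts and a few sentences of protocol text. Because Trial status says that recruitment is under way, some early follow-ups may lack the new items. Their number should be reported by arm alongside the results.
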